### Interim analyses {21b}

A group-sequential approach is planned for the analysis of the primary endpoint, whereby only a futility stop is planned for the interim analysis based on the preliminary data. The studies by Berry and Mok both showed a mean difference in ESS of 2 points in the group with relevant daytime sleepiness (ESS at baseline > = or > 10) and thus in the clinically relevant inferior range [6]. For this reason, it should be possible to terminate the study prematurely if this clinically relevant inferiority was demonstrated. This interim analysis is planned after 300 evaluable patients. At this point, the power is 80% to demonstrate clinically relevant inferiority, i.e. $${H}_{1}:{\mu }_{SPT}-{\mu }_{CPAP}>1.35$$, using a one-sided test at a significance level of 2.5%, assuming that the true effect is a 2-point difference in ESS. The corresponding 2.5% quantile for the standardised test statistic then serves as the futility limit.

The introduction of the futility limit reduces the significance level for the test of the primary hypothesis only insignificantly, so that adjustment is not necessary. This interim analysis therefore does not change the maximum number of cases, but it is possible to terminate the study prematurely if there is a clear effect in the SPT’s disadvantage.

### Methods for additional analyses (e.g. subgroup analyses) {20b}

The following subgroups should be considered: Mild OSA (AHI 5– < 15) vs. moderate OSA (AHI 15– < 30). The analyses in the subgroups are performed analogously to the analyses of the overall population.

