**Methods:**

This is a multicentre, non-inferiority, open-label randomised, cross-over clinical trial. Patients with mild to moderate POSA and daytime sleepiness (according to Epworth Sleepiness Scale (ESS) > 10 points) will be randomised with a 1:1 allocation ratio, stratified by centre and AHI, to start with either PAP therapy or SPT and treated for 12 weeks. After a wash-out period of two weeks, they will switch to the other therapy for 12 weeks. The primary outcome is daytime sleepiness measured by the ESS at the end of each treatment phase. Analysis will be done in the intention-to-treat population using a linear mixed-effects model containing the intervention, the phase, the interaction between therapy and phase (including the carry-over effect) and the baseline measurement of the ESS and AHI as fixed effect, and centre and patient as random effects. A one-sided test at significant level of 2.5% will be used to test the non-inferiority of SPT with a non-inferiority margin of 1.35. Based on a sample size calculation with a one-sided one-sample t-test at significant level of 2.5%, assuming a standard deviation of 4, a total of 418 patients should be included to reach 80% power when SPT is only slightly inferior to PAP therapy (difference 0.8 resulting in a delta of 0.55 (1.35-0.8)). Assuming a 5% drop-out rate, 220 patients per sequence should be included. Possible futility stopping is planned at an interim analysis after 300 patients.

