### Sample size {14}

The aim of the study is to show that SPT is not inferior to PAP therapy in terms of daytime sleepiness measured with the ESS. A difference of 1.35 between the two means is proposed as the non-inferiority threshold, i.e. the hypothesis pair:$$H_0:\mu_{SPT}-\mu_{CPAP}\geq1.35\;vs.\;H_1:\mu_{SPT}-\mu_{CPAP}<1.35$$should be tested with a one-sided test at significance level of 2.5%.

This means that under the alternative hypothesis, the ESS value measured under SPT may not be more than 1.35 points higher on average than the ESS value under PAP therapy. The choice of the value for the non-inferiority margin is justified as follows: The study by Crook et al. investigated the size of the clinically relevant difference for the ESS. Depending on the method used, the difference was between 1 and 4.21 [12]. In other non-inferiority studies, a difference of 1.5 or 2 points was often chosen as the non-inferiority threshold [13]. One meta-analysis showed a difference between PAP vs. no therapy of 2.4 points (95% CI, 1.9 to 2.8) [14]. However, a more recent meta-analysis showed that this difference depends, among other things, on the baseline ESS and AHI. For example, a difference of 1.34 (0.68 to 1.99) was found for a baseline ESS > 10 points and AHI 5 to < 15/h and 2.22 (2.13 to 2.30) for an AHI 15/h to < 30/h [15]. Therefore, the size of the non-inferiority margin of 1.35 provided in the documents of Federal Joint Committee seemed appropriate to ensure at least a difference compared to no therapy in the planned study population.

Hence, sample size calculation was done using a one-sided one-sample *t*-test at a significance level of 2.5% and to achieve a power of 80% to test the above hypotheses. It was assumed that the difference between SPT and PAP is 0.8 points. Sample size calculation for a δ of 0.55 points (1.35–0.8), assuming a standard deviation of 4, results in a required sample size of 418 patients in total, i.e. 209 per sequence. A drop-out rate of 5% is assumed according to the studies by Berry and Mok, i.e. revocation or completely missing data after baseline [6, 13]. Therefore, a total of 440 patients, i.e. 220 per sequence, will be recruited into the study. Further missing values do not affect the sample size, as they will be replaced according to the analysis strategy.

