## Assignment of interventions: allocation

### Sequence generation {16a}

Randomisation sequence (1:1 assignment) was generated using a computer-generated algorithm with randomly selected block sizes stratified by study centre and baseline AHI (mild vs. moderate) using the statistical software R, version 4.1.0 and the R package blockrand.

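### The mild and moderate OSA subgroups are analysed separately with no stated comparison between them, so a split result cannot show whether the SPT–PAP difference depends on severity

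*Protocol article*

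**What the plan says.** The section on additional analyses {20b} of the protocol article names two subgroups, mild OSA (AHI 5 to <15/h) and moderate OSA (AHI 15 to <30/h), and fixes the method: "The analyses in the subgroups are performed analogously to the analyses of the overall population".

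The overall analysis is set out under statistical methods for primary and secondary outcomes {20a}. It is a linear mixed model with fixed effects for therapy, phase, therapy by phase, baseline ESS and baseline AHI, and random effects for centre and patient. It reports an estimated difference, a one-sided confidence interval and a one-sided p-value. The hypothesis behind that p-value, with the 1.35-point margin, "should be tested with a one-sided test at significance level of 2.5" per cent (Sample size {14}). The only interaction listed is therapy by phase; AHI enters as a main effect.

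Randomisation is "stratified by study centre and baseline AHI (mild vs. moderate") (Sequence generation {16a}). The article gives no expected mild/moderate split and no subgroup power. It expressly calls the analyses of secondary endpoints exploratory, but does not say so of the subgroup analyses of the primary endpoint.

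**The concern.** Two questions can be asked of the strata. One is whether SPT is non-inferior within each; the other is whether the SPT–PAP difference changes with severity. Repeating the overall analysis in each stratum addresses the first, with roughly half the patients. It does not address the second, because two separate pass-or-fail results are not a test of their difference. One stratum can meet the margin and the other miss it through sampling error alone.

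The question is a natural one for this trial. AHI class is the only subgroup factor named and a stratification factor, and the trial was commissioned to inform a reimbursement decision (Role of sponsor {5c}). At stake is how the subgroup results are interpreted. The primary estimate, its test and the sample size are unaffected.

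**Working it through.** **Inputs.** All but the split come from Sample size {14}:

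- Margin: "A difference of 1.35 between the two means is proposed as the non-inferiority threshold".
- True difference: "It was assumed that the difference between SPT and PAP is 0.8 points", so the distance to the margin is 1.35 − 0.8 = 0.55.
- SD and N: "assuming a standard deviation of 4, results in a required sample size of 418 patients in total". The test is one-sample, so SD 4 is read as the SD of the within-patient difference.
- One-sided 2.5% level and 80% power.
- Mild/moderate split: not given. Equal strata of 418 / 2 = 209 are an assumption, varied below.

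**Step 1: reproduce the plan's figure.** Exact power of the one-sample t-test (noncentral t, noncentrality 0.55 / (4/√N)) is 79.99% at N = 417 and 80.1% at N = 418. The smallest adequate N is 418, as stated; 418 / 0.95 = 440 also agrees.

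**Step 2: power per stratum.** With n = 209, SE = 4/√209 = 0.277 and 0.55 / 0.277 = 1.988. The normal approximation gives Φ(1.988 − 1.960) = 51.1%; the exact t-test gives 50.7%.

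**Step 3: split results when the effect is the same in both strata.** The strata contain different patients and so are independent: P(exactly one passes) = p₁(1 − p₂) + p₂(1 − p₁). At equal strata this is 2 × 0.507 × 0.493 = 50.0%. Both pass in 25.8% and neither in 24.3%.

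Varying the assumed split of 418, with true difference 0.8 and SD 4:

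| Split | n | Power | Exactly one passes |
|---|---|---|---|
| 50:50 | 209 / 209 | 51% / 51% | 50% |
| 60:40 | 251 / 167 | 58% / 42% | 51% |
| 70:30 | 293 / 125 | 65% / 33% | 55% |
| 80:20 | 334 / 84 | 71% / 24% | 61% |

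Varying the common true difference, with equal strata and SD 4:

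| True difference | Power per stratum | Exactly one passes |
|---|---|---|
| 0 | 99.8% | 0.4% |
| 0.4 | 93% | 13% |
| 0.6 | 77% | 35% |
| 0.8 | 51% | 50% |
| 1.0 | 24% | 37% |
| 1.2 | 8% | 14% |
| 2.0 | about 0% | about 0% |

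At a difference of 0.8 and equal strata, SD 3 gives 37% and SD 5 gives 46%.

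**Step 4: the direct comparison.** At equal strata the SE of the between-stratum difference is 4 × √(1/209 + 1/209) = 0.39, so a 95% CI extends 1.96 × 0.39 = 0.77 points either side. At two-sided 5% the contrast flags a difference in 5% of trials when there is none. In 2 million simulated trials (true difference 0.8 in both strata, normal approximation), exactly one stratum passed in 50% overall and in 57% of trials where the overall test succeeded. About 90% of the split results showed no significant between-stratum difference.

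**The case against.** The strongest reply is that the statistical analysis plan is not shown. The article leaves analysis details to it, and an interaction term is a detail such a plan may well contain. That stands as far as it goes: nobody can say from this article that a difference between strata will go untested. But {20b} does not leave the method open. It prescribes repeating the overall analysis, and an analysis plan that followed it literally would contain no comparison.

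Second, the article states no rule that one stratum passes and the other fails. A reader might infer that the plan itself delivers a finding that SPT works in one severity class and not in the other. The documents do not support that. The subgroups are additional analyses, the single hypothesis pair is for the whole population, and a missed non-inferiority test in a smaller stratum is inconclusive. What remains is that the general rule under Statistical methods classes one-sided p-values at or below 2.5% as significant, so each stratum's p-value would naturally be reported as significant or not.

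Third, a reader might take the cited effects of 1.34 (mild) and 2.22 (moderate) as showing that the plan expects the SPT–PAP difference to vary by 2.22 − 1.34 = 0.88. Those figures compare PAP with no therapy, and the article cites baseline ESS as well as AHI as a determinant. They give no expected SPT–PAP interaction.

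Finally, the contrast can be worked out by hand from the two stratum estimates and their standard errors. That is true, and is a reason to prespecify and report it.

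**Conclusion.** The point holds as a weakness in a stated analysis choice. Separate non-inferiority analyses in mild and moderate OSA cannot show whether the effect depends on severity, and a split result should not be read as a difference.

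A reader might conclude that half of all trials with no true difference between strata would give a split. That is too general. The 50% figure needs a common true difference of 0.8, SD 4 and an equal split. With equal strata 2p(1 − p) cannot exceed 50%, so the design value sits almost exactly at the maximum. The rate falls well below this on either side, and is near zero at the 2-point difference that the Interim analyses section cites from previous studies. Unequal splits raise it at the design value. The range matters more than the single figure, because neither the true difference nor the split is known.

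**What to change.** In {20b}, replace the sentence on analogous analyses with one model fitted to all patients in the primary analysis population. It should be the primary model plus AHI class (mild/moderate as randomised) and a therapy-by-AHI-class term. Report the between-stratum difference in the SPT–PAP effect with a two-sided 95% CI. Take the two stratum estimates and their CIs from the same model. Label the stratum results exploratory, and say that a split against the margin is not evidence of a difference between strata. If the analysis plan already contains this contrast, {20b} need only be brought into line with it.

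The cost is one interaction term and a few sentences; no further data or patients are needed. The drawback is the imprecision shown in the working: the contrast may well be inconclusive, so a non-significant result must not be reported as proof that severity makes no difference.

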### Methods in analysis to handle protocol non-adherence and any statistical methods to handle missing data {20c}

Due to the non-inferiority study, missing values for the primary endpoint resulting from treatment discontinuation and non-completion of the corresponding ESS questionnaire are replaced by the baseline value. In the case of missing values under both interventions, no imputation should be performed, as this is generally anti-conservative in non-inferiority studies. These are therefore omitted from the analysis, and the modified intention-to-treat population is analysed. In addition, sensitivity analyses with the most conservative possible replacement of the missing values under both conditions should be carried out.

The missing values are not replaced for the analysis of the secondary outcomes.

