#### Analysis for the primary and secondary endpoints

The aim of the study is to compare the use of the two therapies in terms of a treatment strategy. The difference in the ESS should therefore be determined without taking into account possible treatment discontinuations or compliance problems. For this reason, the analysis is conducted in a modified intention-to-treat population, which consists of all FAS patients with at least one value of the primary endpoint after baseline.

The *primary endpoint* is analysed using a linear mixed model. The model should contain fixed effects for the intervention, the phase, the interaction between therapy and phase (including the carry-over effect) and the baseline measurement of the ESS as well as the baseline AHI. Both the centre effect and the patient effect are modelled as random effects. The one-sided *p*-value corresponding to the hypothesis specified above, the estimated difference in ESS between the two treatments, and the corresponding one-sided confidence interval are reported. The one-sided *p*-value is calculated from the *p*-value of the above model either as p/2 or as 1-p/2 depending on the sign of the estimator. Details of the model, imputation of missing values, and sensitivity analysis are provided in the SAP.

The *secondary* quantitative endpoints are analysed using analogous models, with the difference that the baseline value of the endpoint under consideration is included in the model as a fixed effect instead of the baseline ESS. Analogous to the analysis of the primary endpoint, the p-value, the estimated difference, and the associated 95% two-sided confidence interval are also specified here. The analysis of dichotomous secondary endpoints is performed using mixed logistic regression models with the fixed effects for therapy, phase, and phase times therapy interaction as well as random effects for centre and patient. The analysis of count data, e.g. AHI, is performed with mixed Poisson models or, if necessary due to overdispersion, with negative binomial models with the fixed effects for treatment, phase, and phase times treatment interaction as well as random effects for centre and patient.

The secondary endpoints are analysed using two-sided tests at a significance level of 5%; all analyses of the secondary endpoints are exploratory.

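### Replacing an ESS value missing under one therapy by baseline is not conservative merely because the trial tests non-inferiority; depending on which values are missing, it can favour SPT

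*Protocol article*

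**What the plan says.** Section {20c} sets the rule for the primary endpoint: "missing values for the primary endpoint resulting from treatment discontinuation and non-completion of the corresponding ESS questionnaire are replaced by the baseline value". It offers the non-inferiority design as the reason. The same section declines to impute when a patient lacks the ESS under both therapies, because imputation there tends to be anti-conservative in a non-inferiority trial. It then plans sensitivity analyses with the most conservative replacement of values missing under both conditions.

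Two other places bear on this:

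- The section on analysis of the primary and secondary endpoints sets a treatment-strategy aim: "The difference in the ESS should therefore be determined without taking into account possible treatment discontinuations or compliance problems".
- Sample size {14} relies on the rule: "Further missing values do not affect the sample size, as they will be replaced according to the analysis strategy".

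Details of imputation and sensitivity analysis are left to the SAP, but the baseline rule and its justification are fixed in the article.

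**The concern.** Setting a value to baseline scores that therapy as having done nothing. If the PAP value is the missing one, the comparator loses its improvement while SPT keeps its own. If similar shares of on-treatment values are replaced under both therapies, a real SPT deficit shrinks towards zero. That is the same danger the section cites when it refuses to impute for patients missing both values. In a non-inferiority test a shift in this direction makes success easier, so the 2.5% error of the confirmatory test is at stake.

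The rule's scope is also unclear. The wording joins discontinuation and non-completion with *and*. It may mean patients who stopped therapy and also gave no ESS. It may instead mean either cause, in which case a questionnaire missed by a patient still on therapy is also set to baseline.

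**Working it through.** **Inputs from Sample size {14}.** Margin: "A difference of 1.35 between the two means is proposed as the non-inferiority threshold". Test: "should be tested with a one-sided test at significance level of 2.5"%. Planning difference: "It was assumed that the difference between SPT and PAP is 0.8 points". SD and N: "assuming a standard deviation of 4, results in a required sample size of 418 patients in total, i.e. 209 per sequence". The PAP effect versus no therapy is 2.4 in one cited meta-analysis.

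**Assumptions.** The article gives no rate of values missing under one therapy and no split between therapies, so 5% to 15% per therapy is assumed. The 2.4 is used as a guide to PAP's improvement from baseline, and 4 as a larger alternative. The SD of 4 is taken as that of the within-patient difference, the reading under which N reproduces.

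**1. The plan's own figure.** The normal approximation (4 × (1.960 + 0.842) / 0.55)² gives 416. The one-sample t-test with the noncentral t gives 418 (power 80.09%), and 418 / 0.95 = 440. The stated figures reproduce.

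**2. Shift caused by the rule.** Let cP and cS be the mean improvements from baseline, with d = cP − cS the true SPT minus PAP difference. Let mP and mS be the shares of patients missing the PAP value only and the SPT value only. After replacement:

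E[SPT − PAP] = cP(1 − mP) − cS(1 − mS) = d − mP·cP + mS·cS

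**3. Error at the margin if the missing values would have been on-treatment values.** Here d = 1.35, cS = cP − 1.35, SE = 4/√418 = 0.196, and error = Φ(−1.96 − shift/SE).

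| Missing PAP / SPT | cP | Shift | One-sided error |
|---|---|---|---|
| 5% / 5% | any | −1.35 × 0.05 = −0.068 | 5.3% |
| 10% / 10% | any | −1.35 × 0.10 = −0.135 | 10.2% |
| 15% / 15% | any | −1.35 × 0.15 = −0.203 | 17.8% |
| 10% / 5% | 2.4 | −0.240 + 0.0525 = −0.188 | 15.8% |
| 10% / 5% | 4 | −0.400 + 0.1325 = −0.268 | 27.7% |
| 5% / 15% | 2.4 | −0.120 + 0.1575 = +0.037 | 1.6% |
| 5% / 15% | 4 | −0.200 + 0.3975 = +0.197 | 0.15% |

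With equal missingness the shift does not depend on cP. The direction reverses once mS/mP exceeds cP/cS: 2.4/1.05 ≈ 2.3, or 4/2.65 ≈ 1.5.

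A simulation of the within-patient t-test (20,000 trials per setting) agrees. Error was 2.3–2.4% with nothing missing and, at cP = 2.4, 5.6% (5% each), 10.2% (10% each), 16.0% (10%/5%) and 1.6% (5%/15%).

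**4. Error if non-completers are off therapy.** Suppose their true ESS is baseline minus r and the treatment-strategy difference is 1.35. Each replaced value is then r points too high, so the shift is (mS − mP)·r.

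- Equal missingness: shift 0, simulated error 2.4–2.6%.
- r = 0: shift 0 for any split.
- 15% PAP / 5% SPT: −0.1 and 7.1% for r = 1; −0.2 and 16.1% for r = 2.

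**5. The sample-size sentence.** A replaced value says nothing about the missing therapy. With 5% missing under each therapy, 418 × 0.90 ≈ 376 patients have both values. On complete pairs, power at the planning difference is Φ(0.55/(4/√376) − 1.96) = Φ(0.71) ≈ 76%, not 80%. A mixed model recovers part of this from single-phase patients.

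**The case against.** A reader might infer that the rule favours SPT whenever PAP values are missing at least as often as SPT values, and that the 2.5% error fails in the most likely pattern of missing data. The article does not support that, for four reasons.

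- **The inflation in step 3 needs improved, on-treatment values to be missing.** If *and* means both conditions together, the replaced patients have stopped therapy. Under the treatment-strategy aim their target is then the off-therapy value. Equal missingness gives no bias, and baseline is right if that is where they return.
- **No pattern can be called most likely.** The article gives neither rate nor split. SPT values may be missing more often, and with a clear enough excess the rule is conservative.
- **The plan limits missing values.** Discontinuers stay on the visit schedule ({11b}), can give the primary endpoint by telephone ({18b}), and outcome fields are mandatory in the eCRF ({19}). At 2% missing under each therapy, even the on-treatment assumption gives a shift of −0.027 and an error of about 3.4%.
- **A missing-at-random model is not always better.** Take missing patients off therapy at baseline level, cP = 4, 5% PAP and 15% SPT missing, and a treatment-strategy difference of 1.35. Then cS = (0.95 × 4 − 1.35)/0.85 = 2.88 and the on-treatment difference is 1.12. An estimate resting wholly on on-treatment values is biased by about −0.23 towards SPT (error about 18–22%), whereas baseline replacement is unbiased.

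All four stand and narrow the point. None of them makes the non-inferiority design a reason for the rule. Off-therapy ESS below baseline is plausible, because entry requires ESS > 10 and regression to the mean follows, though the article does not quantify it. The planned sensitivity analysis does not clearly reach values missing under one therapy only, and it would not change the primary test.

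**Conclusion.** The concern holds in a conditional form. Baseline replacement has no fixed direction: it depends on which therapy loses more values and on what those values would have been.

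- **On-treatment values missing:** at the margin the error is about 5% (5% missing under each therapy), 10% (10% each) and 16% (10% PAP, 5% SPT, PAP improvement 2.4).
- **Non-completers off therapy:** no bias at equal missingness. SPT is favoured only if PAP values are missing more often and the off-therapy level lies below baseline.
- **SPT values missing clearly more often:** the rule is conservative under on-treatment missingness, and also off therapy when the level lies below baseline.

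The formula is firm. The error rates rest on assumed missingness, n = 418, a within-patient SD of 4 and a t-test on paired differences standing in for the mixed model. Separately, the claim that further missing values leave the sample size unaffected is wrong as a statement about information: the 80% power belongs to 418 patients with an ESS under both therapies.

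**What to change.** 1. Remove the non-inferiority design as the justification in {20c}, and state whether a value is replaced after discontinuation with no ESS, or after either event alone.
2. Use all observed ESS values in the primary analysis, including those collected after discontinuation.
3. Do not set questionnaires missed on therapy to baseline. Handle them in the planned mixed model, or by multiple imputation consistent with the treatment-strategy aim. Keep baseline replacement at most for confirmed discontinuers, or as a sensitivity analysis.
4. Add a sensitivity analysis for values missing under one therapy only: worsen missing SPT values step by step to a tipping point, while imputing missing PAP values as observed PAP.
5. In Sample size {14}, say that the 80% power refers to 418 patients with ESS under both therapies and that further missing values reduce the information.

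The cost is a wording change in protocol and SAP, some extra analysis and a slightly lower effective n. It should be settled before the database is closed.
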